### Tertiary outcomes

**
*1. Haemorrhage quantification by e-ASPECTS versus expert human readers.*
** We will use all RITeS NECT containing acute haemorrhage for this analysis. This includes scans acquired from haemorrhagic stroke trials (i.e. brain haemorrhages with or without intraventricular extension) in addition to scans classed as mimics in ischaemic stroke trials (e.g. subdural or subarachnoid haemorrhages).

Haemorrhage will be quantified by location and extent as follows.

*Haemorrhage location*

Haemorrhage location will be defined by side and gross anatomical regions of the brain affected including cerebral lobes (i.e. frontal, parietal, temporal, occipital), basal ganglia, brainstem, cerebellum, or extra-axial compartment (i.e. intra-ventricular, subarachnoid, subdural, extra-dural). We will convert e-ASPECTS haemorrhage detection overlay to these same 22 (11 per side) categories following visual review, blinded to human-reader results.

We will look at differences in the regions (and their number) identified by expert humans and e-ASPECTS and if the data are amenable, consider using methods that account for multiple concurrent haemorrhage sites per patient^52^.

*Haemorrhage extent*

Haemorrhage extent will require a comparison of haemorrhage volume calculated at the voxel level (e-ASPECTS) and haemorrhage dimensions used to estimate volume (i.e. the ABC/2 score^21^,^53^, human readers). We will use Bland-Altman testing (expected range of agreement to be within ± 10 mm^3^) and K-alpha statistics to test agreement between e-ASPECTS and human-rated results.

**
*2a. Impact of e-ASPECTS on diagnostic confidence and treatment decisions.*
** We will invite stroke and hospital admission physicians with a range of experience to complete an online questionnaire including RITeS NECT and relevant clinical scenarios, similar to previous work conducted by RITeS members^1^,^54^. We will compare responses for readers before and after ASPECTS is calculated (i.e. with and without e-ASPECTS overlay) to assess whether ASPECTS alters confidence in stroke diagnosis and determine its influence on management decisions.

RITeS cases with the following range of relevant radiological findings will be selected: with obvious, subtle and no ischaemic brain lesions (and a range of ASPECTS results); with and without hyperattenuating arteries; with subtle brain and extra-axial haemorrhage; with and without pre-stroke brain changes.

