The questionnaire will contain 24 cases including some repetition of the same NECT with and without e-ASPECTS overlay. Specifically, we will include 10 cases shown with and also without e-ASPECTS overlay. To limit reader recognition of repeat cases, these images will be modified (e.g. left-right reversal, removal of any visible extracranial image components) and presented in a non-sequential order. We will also include two unique cases with and two unique cases without e-ASPECTS overlay; each of these 4 cases will be displayed only once. Thus 12 cases will be presented with and 12 without e-ASPECTS overlay. A unique clinical history will be provided for all 24 cases but we will limit clinical variability between repeat cases with and without e-ASPECTS overlay. Each case will include a panel of JPEG images representing the whole brain. Repeat images with and without e-ASPECTS overlay will include identical slices.

We will include up to three questions for each case:

1. Is the e-ASPECTS overlay helpful?• Yes• No2. Given the clinical history and the images presented, would you• Treat the patient immediately with IV alteplase (+/- refer for thrombectomy where available)• Refer the patient immediately for thrombectomy without IV alteplase• Not treat the patient with IV alteplase or thrombectomy but transfer to the acute stroke ward• I’m not sure, I’d first ask for a neuroradiology opinion• I’m not sure, I’d like to do more imaging such as angiography, perfusion imaging or MRI (not available here)3. How confident are you with this decision?• Very unsure• Unsure• Sure• Very sure

We will present these results as per Table 9, and visually in bar charts. We will compare results for the following subgroups in univariable analysis (chi-squared statistics): with versus without e-ASPECTS overlay, more versus less experienced readers, obvious versus subtle or no ischaemic lesion, with versus without haemorrhage, with versus without hyperattenuated arteries, with versus without leukoaraiosis, atrophy or old stroke lesions.

**
*2b. Use of e-ASPECTS/e-CTA and time required for scan interpretation.*

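### Tertiary outcome 2a: read as written, the with-versus-without overlay comparison includes four scans shown in one condition only, so one-sixth of each arm is confounded with scan

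*SAP article*

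**What the plan says.** Under Tertiary outcomes, 2a, the SAP article gives the aim as a before-and-after contrast: "We will compare responses for readers before and after ASPECTS is calculated (i.e. with and without e-ASPECTS overlay". The scans are deliberately varied: "with obvious, subtle and no ischaemic brain lesions (and a range of ASPECTS results); with and without hyperattenuating arteries", with haemorrhage and pre-stroke changes also represented.

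The layout is then set out in four statements:

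- On the total number of displays: "The questionnaire will contain 24 cases including some repetition of the same NECT with and without e-ASPECTS overlay".
- On the scans that serve as their own control: "Specifically, we will include 10 cases shown with and also without e-ASPECTS overlay".
- On the scans that have no counterpart: "We will also include two unique cases with and two unique cases without e-ASPECTS overlay; each of these 4 cases will be displayed only once".
- On the resulting number per condition: "Thus 12 cases will be presented with and 12 without e-ASPECTS overlay".

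The analysis is one sentence: "We will compare results for the following subgroups in univariable analysis (chi-squared statistics): with versus without e-ASPECTS overlay", followed by other subgroup splits. Table 9 reports counts and percentages in With and Without columns, with an absolute difference, 95% CI and p-value. Neither the text nor the table says which displays enter the overlay comparison. Nothing matches or adjusts for scan, and nothing rotates overlay status across readers.

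On clinical histories: "A unique clinical history will be provided for all 24 cases but we will limit clinical variability between repeat cases with and without e-ASPECTS overlay". The safeguards for comparability (limited clinical variability, identical slices) are given for the repeated scans only.

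**The concern.** The question is whether the overlay changes what a reader decides, and how confidently, on a given scan. The ten repeated scans answer it, because each serves as its own control. The four single-display scans cannot: two are seen only with the overlay and two others only without, so for these four overlay status and scan cannot be separated. Since the set was chosen to run from no lesion to obvious lesion and to include haemorrhage, treatment answers can be expected to differ between scans whatever the overlay does.

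If all 24 displays go into the planned comparison, that difference between scans is reported as overlay effect. It is fixed by which four scans are chosen, so recruiting more readers narrows the confidence interval around a wrong value. This is the plan's test of whether the overlay alters decisions and confidence, and it is to be published separately.

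**Working it through.** **1. Counts (Tertiary outcomes, 2a).** Per condition: 10 + 2 = 12. Displays: 2 × 10 + 2 + 2 = 24. Distinct scans: 10 + 4 = 14. The plan's 12, 12 and 24 are reproduced. Unmatched share of each arm: 2/12 = 16.7%.

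**2. Expected difference when the overlay has no effect.** Let p be the mean probability of a given answer over the ten repeated scans, u₁ the mean over the two overlay-only scans and u₀ the mean over the two no-overlay-only scans. With the same number of readers for every display:

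D = (10p + 2u₁)/12 − (10p + 2u₀)/12 = (2/12) × (u₁ − u₀)

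The number of readers does not appear in D. The documents do not give u₁ − u₀, so a range is shown:

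| Assumed gap u₁ − u₀ (points) | Spurious overlay effect D (points) |
|---|---|
| 10 | 1.7 |
| 20 | 3.3 |
| 30 | 5.0 |
| 40 | 6.7 |
| 60 | 10.0 |
| 100 (bound) | 16.7 |

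**3. False-positive rate for a fixed gap.** Simulation of the uncorrected chi-squared test at two-sided 5%, with no overlay effect. Assumptions: the ten shared scans have response probabilities from 0.1 to 0.9, and responses are independent given the scan. The number of readers is also assumed, since the plan gives none for the questionnaire.

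| Readers | 20-point gap, 12 v 12 | 40-point gap, 12 v 12 | Ten repeated scans only |
|---|---|---|---|
| 20 | 8% | 29% | 2-3% |
| 50 | 18% | 66% | 2-3% |
| 100 | 35% | 93% | 2-3% |
| 200 | 66% | 99.9% | 2-3% |
| 500 | 97% | 100% | 2-3% |

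For the 40-point gap the mean pooled difference stays at 6.7 points in every row. On the ten repeated scans it is about zero. The rate there is below 5% because the test ignores the pairing.

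**4. False-positive rate if the scans are random draws.** Here all 14 case-level probabilities come from an assumed distribution with standard deviation s. D is the sum of two probabilities minus the sum of two others, divided by 12, so SD(D) = √(4s²)/12 = s/6. For a uniform distribution s² = 1/12, so SD(D) = √(4/12)/12 = 0.048. At 100 readers:

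| Assumed distribution | SD of D (points) | Draws with D of 5 points or more, either direction | Significant, 12 v 12 | Significant, ten repeated scans |
|---|---|---|---|---|
| Beta(0.5, 0.5) | 5.9 | 42% | 54% | 1% |
| Uniform | 4.8 | 31% | 45% | 2% |
| Beta(1, 2) | 3.9 | 21% | 39% | 3% |
| Beta(2, 2) | 3.7 | 19% | 35% | 3% |
| Beta(2, 6) | 2.4 | 4% | about 23% | 4% |

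Under the uniform distribution the 12 v 12 rate is 31% at 50 readers and 58% at 200. Under Beta(2, 6) with 20 readers it is 8%.

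**5. What restriction leaves behind.** The ten pairs share a scan but not a history. If histories shift the response by an SD of 5 points per display (assumption), the ten-scan difference has a reader-independent SD of 5 × √20/10 = 2.2 points.

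**The case against.** - **The plan does not say that the four scans enter the overlay comparison.** This is correct. The 12 and 12 are counts of displays, and the analysis sentence gives no denominator. The before-and-after aim points to the repeated scans, and the four are introduced just after measures to stop readers recognising repeats, so they may be meant as distractors. A reader might infer that the plan expressly orders pooling; the wording does not go that far. Still, an unrestricted comparison, a 12/12 count and plain With/Without columns make pooling the natural reading.
- **A different test would remove the problem.** This stands in part. A test paired on scan within reader, such as McNemar, drops the unmatched scans, and with scan fixed effects they carry no information on the overlay. Clustering by reader alone would not help. The planned test is neither paired nor adjusted for scan.
- **The false-positive rates are hypothetical.** This stands. Scans are to be selected for their findings, not drawn at random, and the two unmatched pairs could be balanced by choice. Table 9 has three decision rows and four confidence rows, so a mean probability of one half cannot hold in all of them. Less dispersed assumptions give lower rates.
- **Not every row of Table 9 is affected.** This stands. Whether the overlay was helpful has no meaningful answer without an overlay, so the point concerns only the decision and confidence rows.
- **It is a tertiary outcome, and five-sixths of each arm is matched.** This stands and limits the importance of the point. It does not remove the bias.

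**Conclusion.** The point holds as a flaw in how the overlay comparison for tertiary outcome 2a is specified. Followed as written, it puts one-sixth of any difference between unmatched scans into the estimated overlay effect on decision and confidence. The 2/12 weight and the 16.7-point bound follow from the plan's own counts, given equal reader numbers per display. The effect would vanish only if the two unmatched pairs happened to draw the same mean response.

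The realised size is not known. Effects of 3.3 to 6.7 points correspond to assumed gaps of 20 to 40 points. The range of about 23-54% for false significance rests on 100 readers, random draws and the five distributions tried; it is not a property of the plan. A reader might also infer that the study's main conclusions are at risk. They are not: no primary or secondary outcome uses these data.

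**What to change.** State in the text of 2a and in a note to Table 9 that the overlay comparison for decision and confidence uses only the ten scans shown in both conditions. It is preferably analysed as paired on scan within reader, for example by McNemar's test or a mixed model with reader and scan effects. State also that the four single-display cases serve as distractors and are used only for the other subgroup comparisons and the question on whether the overlay was helpful.

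The cost is one or two sentences, and 20 rather than 24 responses per reader in this comparison. The change removes the confounding with scan. It does not remove the difference in history within each repeated pair, which should be acknowledged when the results are reported.

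### Questionnaire 2a changes the clinical history along with the overlay in each repeat pair, leaving a history-related error of unstated size and unknown sign that more readers cannot reduce

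*SAP article*

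**What the plan says.** The design is in the SAP article under Tertiary outcomes, 2a (impact of e-ASPECTS on diagnostic confidence and treatment decisions).

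- Displays: "The questionnaire will contain 24 cases including some repetition of the same NECT with and without e-ASPECTS overlay". Of these, "we will include 10 cases shown with and also without e-ASPECTS overlay". The rest are singles: "We will also include two unique cases with and two unique cases without e-ASPECTS overlay". The split is stated as "Thus 12 cases will be presented with and 12 without e-ASPECTS overlay".
- Histories: "A unique clinical history will be provided for all 24 cases". The same sentence adds a safeguard: "we will limit clinical variability between repeat cases with and without e-ASPECTS overlay". No matching criterion or tolerance is given.
- Images: "Repeat images with and without e-ASPECTS overlay will include identical slices". Repeats are disguised, for example by left-right reversal, and are not shown in sequence.
- Decision question: it opens "Given the clinical history and the images presented, would you".
- Analysis: responses with and without the overlay are compared by univariable chi-squared tests. The stated purpose is to find out whether ASPECTS alters confidence and influences management.

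The section gives no reader number for this questionnaire and does not mention more than one version of it.

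**The concern.** The ten repeated scans are the controlled part of this experiment: the same slices are seen with and without the overlay. That control is incomplete if the history also differs between the two showings, because readers are told to base the decision on the history as well as the images. A reader may decide differently because of the overlay, because of the history, or both.

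As described, each history belongs to one overlay condition only. The history difference is then the same for every reader, so recruiting more readers narrows the confidence interval around a value that includes it. The planned test has no term for pair or history. Adding a history term would not help either, because each history occurs under one overlay condition only.

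At stake is whether a modest difference in decisions or confidence, with versus without the overlay, can be read as an effect of e-ASPECTS.

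**Working it through.** **The plan's own counts.** 10 × 2 + 2 + 2 = 24 displays, and 10 + 2 = 12 per condition. Both agree with the plan. Since all 24 displays have their own history, both members of every pair are included, so the history differs within all ten pairs.

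**Fixed error.** Let d be the shift in the proportion treating between the two histories of a pair, with mean zero and SD σ across pairs. Averaged over ten pairs, the overlay contrast carries an error with SD σ/√10. The number of readers does not enter. The plan gives no σ, so a range from zero is assumed.

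**Sampling error.** With R readers and ten pairs there are 10R responses per condition. Taking a proportion of 0.5 and independent responses, SE = √(2 × 0.25 / 10R). R is assumed.

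- R = 20: √(0.5/200) = 0.050, or 5.0 points
- R = 200: √(0.5/2000) = 0.0158, or 1.6 points

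Total error is √(fixed² + sampling²), all in percentage points:

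| Assumed σ | Fixed error SD | Total, 20 readers | Total, 200 readers |
|---|---|---|---|
| 0 | 0 | 5.0 | 1.6 |
| 5 | 5/3.162 = 1.6 | 5.2 | 2.2 |
| 10 | 10/3.162 = 3.2 | 5.9 | 3.5 |
| 20 | 20/3.162 = 6.3 | 8.1 | 6.5 |

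With few readers or close matching the history error adds little. With many readers it equals sampling error at σ = 5 and dominates at larger σ.

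**Check by simulation.** The true overlay effect was set to zero and the ten pairs were analysed with the planned unadjusted chi-squared test at 5%, with 1000 replicates per setting. On the logit scale the assumed SDs were 0.5 for readers, 1.0 for images and s for each history. In the first block each history is tied to one overlay condition, as the plan describes.

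| s | SD of overlay difference, 20 / 50 / 200 / 1000 readers | False positives |
|---|---|---|
| 0 | 0.042 / 0.028 / 0.015 / 0.006 | 2% / 3% / 3% / 2% |
| 0.25 | 0.049 / 0.035 / 0.027 / 0.023 | 5% / 9% / 26% / 53% |
| 0.5 | 0.063 / 0.053 / 0.048 / 0.044 | 12% / 24% / 53% / 74% |
| 1.0 | 0.088 / 0.085 / 0.081 / 0.083 | 27% / 47% / 72% / 87% |

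To relate s to σ: at s = 0.25 and 1000 readers, removing sampling error leaves √(0.0228² − 0.0061²) = 0.022, and 2.2 × √10 is about 7 points. That row therefore lies between σ = 5 and σ = 10.

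When histories were swapped at random between overlay conditions for each reader and pair, the SD fell with reader number at every s (about 0.045, 0.028, 0.014 and 0.006). False positives stayed between 2.7% and 4.0%.

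**The case against.** The plan foresees the problem. The sentence that assigns unique histories also commits to limiting the clinical differences between repeats, and the slices are identical. Different histories help to hide the repeats, and a reader who recognised a repeat would spoil the comparison in another way. A left-right reversed image may itself call for a changed symptom side, so unique need not mean very different. With close matching and few readers the harm is small: at s = 0.25 and 20 readers the simulated false-positive rate is 5%. All of this stands, and it is why the range has to start at zero.

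The article also does not say outright that every reader receives the same pairing, and details of the online build may be held elsewhere. That is fair. If histories are already swapped between readers, the concern falls away. The article as written describes a single questionnaire and a pooled test that would not use such swapping.

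The pooled contrast also includes the four single cases. They do not help, because between conditions they differ in scan as well as in history. Whether readers find the overlay helpful needs no with-versus-without contrast and is unaffected.

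A reader might infer that the overlay effect is systematically biased, or that no difference could ever be attributed to e-ASPECTS. The documents do not support that. Nothing suggests that the histories lean one way across the ten pairs, and without a consistent direction the result is extra error of unknown sign. Nor do they support treating an error of 3 to 6 points as established, since the plan states neither the closeness of matching nor the number of readers.

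**Conclusion.** The concern holds in a limited form. Within each of the ten pairs the history changes along with the overlay. The plan limits the difference without saying how closely, and it describes no swapping across overlay conditions. The contrast therefore carries a history-related error that more readers on the same 24 displays cannot reduce.

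Its SD is 0 to 6.3 points for an assumed between-history SD of 0 to 20 points. Whether it matters depends on reader numbers: it is minor beside a sampling error of 5 points at 20 readers, but equal to or larger than the 1.6 points at 200 readers once the between-history SD reaches 5 points. The between-history SDs, the reader numbers and the simulation SDs are all assumptions.

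Severity is low. The outcome is tertiary, it is to be reported after the primary publication, and no primary or secondary result depends on it.

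**What to change.** Build two versions of the online questionnaire. For each of the ten pairs, keep history, image orientation and position together as one display, and switch only which of the two displays carries the overlay: the first in version A, the second in version B. Allocate readers to a version at random. Each history is then seen both with and without the overlay, and the repeats stay hidden.

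Replace the pooled chi-squared test for the overlay contrast with an estimate on the ten pairs that accounts for pair, reader and version, for example a mixed logistic model for the decision and an ordinal one for confidence. Accounting for version matters because unequal numbers of readers per version would otherwise leave part of the history difference in the estimate. Report the four single cases separately. State in the plan how closely paired histories are matched.

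The cost is one extra build, with the overlay prepared for both displays of each pair, a random link and a slightly more complex analysis. No further readers or scans are needed. It must be done before responses are collected, because later analysis cannot separate history from overlay if every reader saw the same pairing.

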## Introduction

Accurate and rapid identification and quantification of CT imaging features indicative of early ischaemic and haemorrhagic stroke is required to correctly triage patients for urgent treatment. However, early ischaemic brain changes can be subtle on non-enhanced CT (NECT) and identification requires training and experience^1^. The Alberta Stroke Program Early CT Score (ASPECTS) helps quantify early ischaemia on CT and may aid decision making prior to thrombolysis and thrombectomy^2^–^4^. It is particularly important to exclude acute intracranial haemorrhage as the cause of stroke prior to thrombolytic therapy since thrombolysis may worsen haemorrhage. Additionally, a CT angiogram (CTA) may be required immediately after NECT to identify patients with arterial obstruction who are suitable for thrombectomy. Interpretation of CTA also requires training and experience.

A potential solution to help interpret brain CT and CTA after suspected stroke is offered by e-ASPECTS and e-CTA diagnostic software (Brainomix Ltd, Oxford UK). This software, developed using machine learning, includes an automated ASPECTS and detection of acute haemorrhage on NECT, and a CTA assessment to detect large vessel obstruction (LVO) and collateral blood supply. e-ASPECTS is said to be as accurate as expert human rating of ASPECTS^5^,^6^, and the software has been promoted to support and accelerate stroke treatment decisions. However, as is the case with many diagnostic tools developed using machine learning^7^, e-ASPECTS lacks independent demonstration of reliability, safety or clinical utility, especially for newer features of haemorrhage detection and CTA assessment^8^. It is also unclear how e-ASPECTS handles other pathologies which make up around 20% of patients presenting with stroke-like symptoms (i.e. stroke mimics) such as tumours, subdural haematomas or infections.

The Real-world Independent Testing of e-ASPECTS Software (RITeS) study will independently evaluate the accuracy, reliability and clinical benefit of e-ASPECTS and e-CTA software. Here we pre-specify the statistical analysis plan for RITeS.

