### Tertiary outcomes

1. Difference in haemorrhage size and location results provided by e-ASPECTS versus expert human readers.2. Potential clinical impact of e-ASPECTS and e-CTA on routine acute stroke care, whether: a. knowledge of ASPECTS conveyed using e-ASPECTS visual overlay on imaging influences diagnostic confidence or alters treatment decisions,b. use of e-ASPECTS/e-CTA alter the time required for scan interpretation, andc. e-ASPECTS or e-CTA results are associated with outcome after ischaemic stroke.

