**TOTAL**			

**Note:** All results n (%). Proximal = ICA or proximal MCA (M1). Distal = distal MCA (M2+).

**Table 7. T7:** Options for comparing modified Tan (e-CTA) and Miteff methods (human rated) of MCA collateral scoring.

Modified Tan used by e-CTA to grade collaterals	Miteff comparison 1	Miteff comparison 2	Miteff comparison 3
3 = Excellent (>90%)	Good	Good	Good
2 = Good (50–90%)		Moderate	Moderate
1 = Poor (10–50%)	Moderate		Poor
0 = None (0–10%)	Poor	Poor	

**Table 8. T8:** Planned results for e-ASPECTS and e-CTA repeatability testing.

Tested Component	Result
e-ASPECTS, ischaemia	N, % with matched ASPECTS results
	N, % for each of 1–10 point ASPECTS difference
	Median, IQR for difference in scores
e-ASPECTS, haemorrhage	N, % with matched location results
	N, % for each of 22 named regions
	Median, IQR for comparison of haemorrhage volumes
e-CTA, obstruction	N, % with matched ICA-MCA proximal vs distal results
e-CTA, collateral scoring	N, % with matched collateral scores
	Median, IQR for comparison of collateral scores

Note: ICA = internal carotid artery. MCA = middle cerebral artery.

**Table 9. T9:** Planned results for effect of e-ASPECTS on diagnostic confidence and treatment decisions questionnaire.

Question	Total, n (%)	Subgroups: e-ASPECTS overlay, reader experience, visible ischaemic lesion, haemorrhage, hyperattenuating arteries, leukoaraiosis, atrophy, old stroke lesions		Absolute differences, 95% CI and p-value
		With n (%)	Without n (%)	
Found e-ASPECTS overlay helpful				
Decision				
Treat patient with thrombolysis/ thrombectomy				
No acute treatment				
Request further radiological input				
Confidence in decision				
Very unsure				
Unsure				
Sure				
Very sure				

Note: Table truncated for presentation of subgroups.

**Table 10. T10:** Planned ordinal regression analysis results with 3–6-month post-stroke outcome as dependent variable.

Variable	Raw Data N (%) or Median (IQR)	Odds Ratio, OR	95% Confidence Interval	p-value
Age, years				
NIHSS				
Time from stroke onset, minutes				
Treated with alteplase +/- thrombectomy				
Software-derived result *				

Note: NIHSS = National Institutes of Health Stroke Scale, IQR = Inter-quartile range. * Either ASPECTS result, presence/absence of ICA-MCA axis occlusion, MCA collateral score.

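### Tertiary outcome 2a: the questionnaire cannot record thrombectomy referral being added or dropped alongside alteplase, and Table 9 merges other answers that are recorded separately

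*SAP article*

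**What the plan says.** The Tertiary outcomes list in the SAP article sets the aim of 2a: whether knowing ASPECTS through the overlay "influences diagnostic confidence or alters treatment decisions". The Introduction states that ASPECTS "may aid decision making prior to thrombolysis and thrombectomy", naming the two treatments separately.

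The treatment question (the second of up to three per case, Statistical analysis, Tertiary outcomes, 2a) has five answers:

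1. "Treat the patient immediately with IV alteplase (+/- refer for thrombectomy where available" (the bracket closes there)
2. "Refer the patient immediately for thrombectomy without IV alteplase"
3. "Not treat the patient with IV alteplase or thrombectomy but transfer to the acute stroke ward"
4. unsure, would first seek a neuroradiology opinion
5. unsure, would want further imaging such as angiography, perfusion imaging or MRI

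Table 9 has three decision rows for these five answers: "Treat patient with thrombolysis/ thrombectomy", "No acute treatment" and "Request further radiological input". Each row shows n (%) for the two subgroup arms, with an absolute difference, confidence interval and p-value. The text says results will follow Table 9 and also appear in bar charts, and that subgroups, including overlay shown or not shown, will be compared by chi-squared statistics. It does not say which answer categories the bar charts or the chi-squared comparisons use.

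**The concern.** An instrument meant to show whether the overlay alters treatment decisions has to separate the decisions the overlay might alter. By the plan's own account, thrombectomy is one of them. Besides the Introduction, the primary-outcome section uses an ASPECTS 0-5 versus 6-10 cut-point with the same citation that the patient-sample section attaches to the pooled thrombectomy trials. The primary-outcome section also justifies its limit of agreement by saying that such a difference might alter treatment at those thresholds.

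If thrombectomy referral changes in a patient who would receive alteplase either way, answer 1 does not show it. If the reader moves between answers 1 and 2, Table 9 does not show it. A small difference in the active-treatment row could then be reported as the overlay having no influence on treatment, when part of that influence was not recorded or not tabulated.

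**Working it through.** The plan's only count in this part is the number of cases: 10 cases shown both ways, plus 2 shown only with and 2 only without the overlay. That gives 10 × 2 + 2 + 2 = 24, with 10 + 2 = 12 per condition, as stated. The point does not depend on it.

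The check maps each decision a reader may intend to its answer and its Table 9 row.

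| Intended decision | Answer | Table 9 row |
|---|---|---|
| Alteplase, no thrombectomy referral | 1 | active treatment |
| Alteplase with thrombectomy referral | 1 | active treatment |
| Thrombectomy referral, no alteplase | 2 | active treatment |
| Neither | 3 | no treatment |
| Unsure, neuroradiology opinion | 4 | further input |
| Unsure, more imaging | 5 | further input |

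Six intended decisions become five answers and then three rows.

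**Changes in thrombectomy referral between definite decisions.** Two of the four definite decisions include referral and two do not, so there are 2 × 2 = 4 kinds of change:

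| Change | Questionnaire | Table 9 |
|---|---|---|
| Alteplase alone ↔ alteplase with referral | lost (1 and 1) | lost |
| Alteplase alone ↔ thrombectomy without alteplase | kept (1 and 2) | lost |
| Neither ↔ alteplase with referral | kept (3 and 1) | kept |
| Neither ↔ thrombectomy without alteplase | kept (3 and 2) | kept |

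Lost: 1 of 4 in the questionnaire and 2 of 4 in Table 9. Counting the two unsure answers as not referred adds 2 × 2 = 4 further kinds of change. All of these are kept in both places, so the counts become 1 of 8 and 2 of 8.

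**All kinds of change.** Six intended decisions give 6 × 5 / 2 = 15 pairs. The questionnaire loses 1. Table 9 loses the 3 pairs inside the active-treatment row and the 1 pair inside the further-input row, 3 + 1 = 4 in all. Of these 4, 4 − 1 = 3 can be recovered from the raw answers; the remaining one cannot.

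**After the split.** With six answers and one row for each, 0 of the 15 pairs share an answer or a row.

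These figures count kinds of change, not how often each occurs. The document gives no expected frequencies and no number of questionnaire readers.

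**The case against.** A reader might infer that any overlay-driven change in the thrombectomy decision will be recorded as no change. The document does not support that. Thrombectomy without alteplase has its own answer, and a move between no treatment, or an unsure answer, and any active treatment shows in both the questionnaire and Table 9.

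A reader might also infer a count of hidden decisions. None can be given: the plan states neither the number of questionnaire readers nor a switching rate. Nor does it score pairs as changed or unchanged, because Table 9 compares percentages between the two conditions.

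The strongest defence is that the bundling is deliberate. Readers see only non-enhanced CT, and the plan says elsewhere that CTA may be needed to identify patients suitable for thrombectomy. A referral made at this stage may be provisional, and a reader who wants angiography can choose answer 5. The bracketed wording also lets readers with and without local thrombectomy tick the same box, so it need not create dependence on local services. This has some weight. But the questionnaire itself offers immediate thrombectomy referral as answer 2, so it treats that decision as answerable from these images. A shared box also leaves unknown whether referral was meant.

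Bar charts or chi-squared tests on all five answers would recover what Table 9 merges. The plan does not say they will be done that way, and they could not separate the two decisions inside answer 1. The note that Table 9 is truncated refers to subgroups and does not promise more decision rows.

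**Conclusion.** The point holds in a limited form, with two losses of different weight.

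- **Data capture:** referral added or dropped alongside alteplase is not recorded and cannot be recovered afterwards. This is one of four kinds of change in referral between definite decisions.
- **Reporting:** a switch between answers 1 and 2, or between the two unsure answers, is recorded but disappears in Table 9. The planned table therefore hides two of the four kinds of referral change, one of them already lost at capture.

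This rests on reading the Table 9 rows as groupings of the five answers, which their labels leave little room to doubt. How many answers would be affected is unknown. The outcome is tertiary and is to be reported separately after the primary publication, so no primary or secondary result is affected. The change is still worth making because the plan says the tertiary outcomes need additional data to be collected. The first loss becomes permanent once the questionnaire has run in its present form.

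**What to change.** Before the questionnaire is launched:

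- Split the first answer into alteplase without thrombectomy referral and alteplase with thrombectomy referral, and give all readers the same instruction on what availability to assume.
- Give each answer its own row in Table 9, and state that the comparison of overlay shown with overlay not shown uses those same categories.
- Keep the merged active-treatment row as a secondary summary.

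The cost is one more answer (six instead of five) and smaller cells in the table and the chi-squared comparisons. If the questionnaire has already run, only the Table 9 part can be repaired, by tabulating the five recorded answers and stating that answer 1 does not distinguish referral. The change concerns how decisions are recorded and reported; it takes no position on which treatment is right for any case.
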